#### 4. Personal pilot

The personal pilots are the first point of contact for all patients who are admitted to the project. Pilots have the qualifications of trained psychologists, social workers/educators, health scientists or health care professionals. They ensure the connection between the project management team providing the outcome from the screening, the specialized clinic conducting the assessment and the patients—both in an anonymized way. A personal pilot is assigned to each patient who was screened positively and who takes part in the study.

The personal pilots contact the patient by phone or email within 4 days after the participant has finished the screening tool. They provide information about the study process. The personal pilot arranges the inpatient assessment in the IG by making the referral to the assessment clinic. In addition, the personal pilot recommends and organizes participation in digital services.

The personal pilot is available throughout the entire process of care, from screening to implementation of the treatment plan. Thus, the pilot supports the patients throughout the entire medical care as a contact point for both the patients and the medical service providers involved. At regular intervals, they contact the study participants in order to reflect on the progress, make qualitative notes of their observations with the patients (e.g., whether there was anything special or unusual to discuss, or what else patients need or want beyond the [digital] interventions that are already provided in the study) and try to motivate the patients also to increase the study commitment of the patients. Their final aim is to empower patients in their coping with PACS and enable them to find and make use of the best treatment. In the final discussion at the end of the study participation, the personal pilot gives recommendations for further care. The personal pilots are trained in motivational interviewing [35, 36].

The personal pilot supports the referral to any necessary further diagnostics and therapy in the IG and ACG (e.g., therapies, rehabilitation, aftercare) and helps the patient to identify suitable leisure activities, such as individually appropriate physical exercises, gyms and recreation/fitness centers close to the patient’s home. The pilots help to arrange the appropriate contacts and access to suitable self-help groups. Moreover, the pilot helps to find a general practitioner if none is available yet. The personal pilot serves as an empowering coordinator throughout the entire care process, mediating information to the various service providers in the inpatient and outpatient sectors and the patients not admitted to the study by means of dissemination strategies.

With the use of personal pilots, we will assess the applicability of Hypothesis 4 that a personal pilot can ensure the sustainable management of interdisciplinary treatment. To test this hypothesis, we will use a qualitative approach and ask the personal pilots to what extent patients have engaged in sustainable treatment and what factors in the interaction between the pilots and the patients were especially helpful to foster a sustainable treatment. Accordingly, answers will be analyzed by means of qualitative content analysis [37–39].

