### The Research Project

The objective of the present study is the early detection of post-acute COVID-19 symptoms (PACS) and subsequently a long-term and sustainable holistic care and support of patients with PACS to avoid long-term illness and chronification, and to enable social participation.

The long-term goals of the study are the dissemination of validated instruments (i.e.g., the online screening) and newly developed treatment approaches (i.e., the digital interventions and a  personal pilot concept) through communication to central stakeholders such as medical associations, health insurance companies, service providers in the outpatient and inpatient sector as well as professional societies and care institutions. In this way, patient care is to be improved beyond the project duration and care services are to be made more efficient.

Hypotheses, which will be tested with this project, are the following:A short *screening* can detect the presence of PACS.A comprehensive* assessment* can validly and reliably determine rehabilitation or remedial needs and the leading rehabilitation indication and be basis of an individual multidisciplinary treatment plan.The more *individualization* the digital therapy offers, the higher the effectiveness in the treatment of PACS.As contact point for all involved parties, a *personal pilot * empowering the patient suffering from PACS can -by means of an interdisciplinary and intersectoral treatment planning- ensure the sustainable management of interdisciplinary treatment.An *interdisciplinary treatment pathway* and the personal pilots empower the patients, so that the patients receive the appropriate diagnosis and treatment, and to actively participate in their own recovery, ensuring patients recover quickly and sustainably from their PACS conditions, increase their functional capacity, reduce incapacity to work and regain participation.

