## Methods

### Study design and setting

This longitudinal randomized control trial study will take place in Bavaria in Germany and has three study arms. Specifically, patients will be randomly assigned to an intervention group (IG) or an active control group (ACG, see Fig. 3 for the flow chart). Furthermore, a comparison group (CompG) will be recruited. Whereas the CompG will not receive any treatment, the IG and the ACG will have contacts with a *personal pilot* who will help the patients to navigate the study participation as well as through treatment options and help them seek help for further needs. The personal pilot acts as a contact point for patients and service providers and guides patients through the care process. Furthermore, the personal pilots make sure participants will take part in the study questionnaires by continuously reminding the patients in case they did not fill out the questionnaires.

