### Dissemination of the study results

After completion of the study project, a large network of outpatient and inpatient providers will have been established who offer the treatment to patients with suspected PACS. If the effects of the personal pilot and the digital training interventions transpire successfully, this provides evidence that such a support system may pay off, especially in times of people in need where no services are available at their convenience.

The aim of the current study is to enable the decision-making processes and the evidence-based treatment of PACS patients in the general population with their diverse and individual complaints in the long term, to discharge them from treatment into their everyday lives, and to reintegrate into society. To do so, a *manual* that includes a description of the contact session between the personal pilot and the patient will be made freely available after the completion of the project to ensure continuous and standardized care according to a well-established and valid process for individuals diagnosed with PACS. To ensure the future care for individuals with PACS, any doctor can introduce patients into the treatment pathway; we believe that what is needed is contact with the personal pilot. Service providers who meet the professional and structural requirements for interdisciplinary and holistic assessment and treatment planning in the sense of the bio-psycho-social model can guide the treatment with a high level of quality.

The comprehensive care process should be able to be transferred to regular care and other illnesses and, after the study is completed, will be presented in a corresponding concept (*white paper*) for diagnostics and care specifically for the target group along with the manual for the personal pilots. Our project, which is intended to close a relevant gap in care, has the potential to not only be transferable regionally, but nationwide and internationally.

The results regarding the hypotheses will be disseminated in scientific publications, which will be communicated to experts and the public by means of press work and social media.

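### Hypothesis 4 is worded as an effect of the personal pilot, but its only stated test asks the pilots about their own patients, and no planned comparison isolates the pilot

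*Protocol article*

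**What the plan says.** **The hypothesis.** In The Research Project, Hypothesis 4 states that a personal pilot can "ensure the sustainable management of interdisciplinary treatment". Hypothesis 5 credits the treatment pathway and the pilots together with empowerment and recovery.

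**Its test.** Under 4. Personal pilot: "we will use a qualitative approach and ask the personal pilots to what extent patients have engaged in sustainable treatment". The pilots are also asked which features of their interaction with patients helped. The answers go to qualitative content analysis, and Type of statistical analysis used confirms that Hypothesis 4 has no statistical analysis.

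**Who has a pilot.** Study design and setting: "Whereas the CompG will not receive any treatment, the IG and the ACG will have contacts with a" personal pilot. Under 4. Personal pilot: "A personal pilot is assigned to each patient who was screened positively and who takes part in the study", and "The personal pilot supports the referral to any necessary further diagnostics and therapy in the IG and ACG".

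**What is to be concluded.** The abstract speaks of evaluating the feasibility and applicability of the pilots. Dissemination of the study results says that, if the effects of the pilot and of the digital training turn out well, "this provides evidence that such a support system may pay off". The same section later promises information on effectiveness, as well as acceptability and feasibility, for the different components. Evaluation concept lists the pilot as one of the four components to be evaluated.

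**The concern.** To say that a service can ensure an outcome is to claim an effect. Supporting it needs a comparison in which that service varies and a measure of the outcome that does not depend on the provider's own opinion. The stated test of Hypothesis 4 has neither. The pilots are asked how far patients engaged, although motivating those patients is part of their job, and Blinding confirms that they know the allocation.

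The protocol intends to carry the approach into regular care, nationally and internationally, and to publish a manual for the pilots. If the pilot is promoted as an effective component, that claim would rest on provider accounts and on comparisons of whole packages.

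**Working it through.** No arithmetic beyond an exposure contrast applies. The check is whether any planned comparison varies the pilot alone, and whether the stated test of Hypothesis 4 can bear its wording.

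**Step 1. Components by group** (Study design and setting; 2. Comprehensive assessment program; 3. Digital therapy offers; Evaluation concept)

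| Group | Pilot | 3-day assessment | Digital programme | Entry |
|---|---|---|---|---|
| IG | yes | yes | tailored to physical resilience | randomised |
| ACG | yes | no | tailored to leading symptom | randomised, plus marked patients who could not be randomised |
| CompG | no | no | at most a voluntary chatbot | separate link, not randomised |

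For the CompG, Study design and setting says no treatment, while 3. Digital therapy offers mentions voluntary use of the chatbot. On either reading it has no pilot and no tailored programme.

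**Step 2. What each comparison varies**

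- IG v ACG: pilot exposure 100% − 100% = 0. The arms differ in the assessment and in how the digital programme is tailored.
- IG v CompG: pilot, assessment and digital programme all differ. Propensity score matching is planned for this pair.
- ACG v CompG: pilot and digital programme both differ. Matching is stated only between IG and CompG.

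No row isolates the pilot. The pilots also remind patients to complete questionnaires, so follow-up effort differs between the CompG and the other two groups as well. A statistical analysis plan could not recover a separate pilot effect from these contrasts, because the gap lies in the design.

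**Step 3. The test of Hypothesis 4 against its wording**

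- Claim: the pilot can ensure sustainable management of treatment.
- Stated informants: the pilots, who deliver the service and are unblinded.
- First question: how far patients engaged. This is an outcome, reported by the provider.
- Second question: which interaction factors helped. This is a process question. It takes some benefit as given and does not test whether there was any.
- Comparator: none. Statistical analysis: none.

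The second question suits a qualitative method and these informants. The first does not suit these informants as sole source.

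**Step 4. Other sources already in the plan**

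Evaluation concept has patients answering questionnaires repeatedly, with T4 about 6 weeks after T3 and T5 another 6 weeks later. It also plans interviews or focus groups with participating patients. Their stated purpose is implementation fidelity and dose; no sentence links them to Hypothesis 4.

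**Step 5. Claims side by side**

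The abstract's aim, feasibility and applicability, is one that the design can meet. The wording of Hypothesis 4, the pilot part of Hypothesis 5, and the statements on support-system benefit and component effectiveness under Dissemination of the study results go beyond it.

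**The case against.** The strongest reply is that the protocol claims less than it may seem to. The sentence under Dissemination of the study results is conditional, hedged with *may*, and covers the pilot and the digital training jointly. The abstract already sets a feasibility aim, and Hypothesis 4 is openly a qualitative strand. Evaluation concept sets up one evaluation plan for the four components and five hypotheses, and patient interviews are in it. The measures are in an additional file that is not shown, so items on treatment uptake may already exist. Giving both arms a pilot also holds that component constant, which helps the IG–ACG comparison.

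Most of this stands, and it rules out two stronger readings:

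- A reader might infer that the trial plans to conclude that the pilot by itself works, and that any such conclusion would be empty whatever the data show. The documents do not support that. The sentence is joint and hedged, and the planned comparison of IG, ACG and CompG on symptoms, daily activities, return to work and participation gives some evidence, though weak and non-randomised, on the package. ACG v CompG differs in just that bundle of pilot and digital programme.
- A reader might infer that an IG–ACG difference will be credited to the pilot. No sentence does so, and the section that describes the test of Hypothesis 5 names only the treatment pathway.

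The reply does not remove the mismatch between an *ensure* claim and a test built on the providers' own accounts. It also does not remove the promise of effectiveness information for the separate components.

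**Conclusion.** The point holds as a mismatch between claim and test. Hypothesis 4 is worded as an effect; its only stated test uses the pilots' accounts of their own patients without a comparator; and no planned comparison isolates the pilot. The randomised contrast in pilot exposure is 0. What the CompG adds is a weak, non-randomised estimate of a package.

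This rests on the article's own statements of who receives a pilot and how Hypothesis 4 is tested. It does not assume that uptake items are missing from the questionnaires, which cannot be seen.

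Severity is moderate. The primary endpoints (symptom reduction and return to work) and the randomised comparison are unaffected, so it would be too much to infer that the trial's main result is compromised.

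**What to change.** 1. Reword Hypothesis 4, the pilot part of Hypothesis 5, and the statements on benefit and component effectiveness under Dissemination of the study results. The pilot is evaluated for feasibility and acceptance only. IG v ACG estimates the effect of the assessment-based pathway given a pilot in both arms. Any comparison with the CompG is a non-randomised estimate of the package.
2. State that patients' engagement in sustainable treatment, for Hypothesis 4, is judged from patient-reported uptake and continuation of treatment at T4 and T5 and from the patient interviews already planned. Add items only if the existing questionnaires lack them. Keep the pilots' accounts as process data on which interaction factors helped.

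The second change gives a better measure of engagement but still no pilot effect, so the first is needed as well. The cost is protocol wording, possibly a few questionnaire items and additions to the interview guide, and a more modest claim about pilots. No new arm or larger sample is required.

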### Evaluation concept

A longitudinal randomized control trial design is used in this project with a three-group pretest–posttest procedure. Whereas the CompG will be recruited with different links via online invitations (e.g., via social media campaigns), the IG and the ACG are recruited with another separate link. After agreeing to take part in the study, participants will be randomized by throwing a dice. Patients for whom a 1 or 2 was rolled are placed in the IG and patients for whom a 3–6 was rolled are placed in the ACG. If a randomization cannot be realized (e.g., because they cannot take part in the stationary assessment due to organizational limitations), patients will be allocated to the ACG but will be marked for statistical analyses. Methodically, a propensity score matching will be used between the IG and the CompG to ensure the comparability of these groups (i.e., participants will statistically be matched by various person-related criteria such as age and sex). All groups are repeatedly interviewed with similar instruments in each group (see Table 1). Time points of measurement are the screening (T1), prior to the assessment in the IG and a comparable time point in the ACG (T2), after the assessment in the IG and at a comparable time point in the ACG (T3). Then approximately 6 weeks after T3 and after symptom-specific digital interventions, a further measurement will take place (T4). Another 6 weeks later a follow-up measurement will take place (T5). A last measurement time point (T6) will be conducted 6 months later with some selected participants. All time points of measurement are included in the study flow chart (Fig. 3).

As the project aims to evaluate the four components (online screening, personal pilots, assessment, digital interventions, see Fig. 4) and the five hypotheses that were described above, a structured evaluation plan is set up. The study aims to alleviate or resolve PACS, and thus to generally restore physical and mental functioning. In addition, the aim is to resume performance in terms of activity and social participation. Within the framework of a successful recovery process as described in the CCAM (see Fig. 2), the active cooperation of the patient affected is obligatory. That is, the factors motivation, psychological stability/resilience, and coping strategies will also be considered in the evaluation process. Furthermore, the economic situation and personal contextual factors will also be considered. Different indicators are used to conduct the evaluation process. These include participation/drop-out rates at the different measurement points, acceptance, and satisfaction over the course of participation, implementation fidelity, implementation dose, target group achievement as well as a systematic analysis of the mediating processes.

Focus groups or individual interviews with the clinic staff (at least one person per occupational group) and the participating patients are planned with partially standardized guidelines, which are evaluated with the use of a content analysis. In addition, structured, participatory observations are conducted, and the observations are tracked. The process evaluation is intended to provide information on the implementation fidelity (e.g., which contents were implemented and realized as planned?), and implementation dose (e.g., to what extent were all intended contents covered or implemented? Attendance of participants?).

For the *summative effectiveness evaluation*, the primary endpoint is the symptom reduction regarding PACS, and RTW. Secondary outcomes include social participation, health-promoting behaviors, and activities of daily living (ADL) as well as mental health and life satisfaction/quality of life. Survey and documentation of all endpoints are conducted by means of questionnaires and/or interviews with study participants who have completed interventions over the course of the project as described above. In addition, possible moderators (especially socio-demographic data) and mediators (e.g., motivation, self-efficacy, and coping strategies) are quantitatively reviewed and added to the analyses. An overview of the measures is provided in Table 2 and Additional file 1.

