Secondly, patients will be recruited via the use of media, including regular press releases (approx. once a month after more frequent press releases in the beginning of the recruitment), radio podcasts as well as social media posts on Facebook and Twitter. If 20% click on the link to the website of WHO and 20% take part in the screening, 2500 people with PACS are needed to be reached, to recruit 100 study participants.

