### Statistical analysis

#### Sample size planning

With an alpha error of 0.05 and a power of 68%, a sample of *N* = 132 (*n* = 66 in the IG and *n* = 66 in the ACG) is required to be able to demonstrate an effect of *d* = 0.15. The evaluation will be conducted statistically using a Multivariate Analysis of Variance (repeated-measures MANOVA: within-between interaction; power analysis calculated with G*Power). In addition to classical significance tests (*p*-value of a two-sided test below 0.05), the clinical significance will be calculated with effect sizes.

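### The dice rule allocates 1:2 (IG:ACG), but the sample size assumes 66 per arm, so at N = 132 neither the planned IG nor the stated 68% power is delivered

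*Protocol article*

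**What the plan says.** Evaluation concept sets the randomisation rule: "Patients for whom a 1 or 2 was rolled are placed in the IG and patients for whom a 3–6 was rolled"; the second set of faces leads to the ACG. The same section covers people for whom randomisation cannot be carried out, for example because they cannot attend the clinic assessment: these "patients will be allocated to the ACG but will be marked for statistical analyses".

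Sample size planning gives the target. It opens "With an alpha error of 0.05 and a power of 68" percent, puts the total at 132 with "n* = 66 in the IG and *n* = 66 in the ACG", and says this number "is required to be able to demonstrate an effect of *d* = 0.15". The method is given as "repeated-measures MANOVA: within-between interaction; power analysis calculated with G*Power", with significance judged by a "p*-value of a two-sided test below 0.05".

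Study sample and recruitment describes two routes. The physician route is expected to yield about 100 people for screening. For the media route, "2500 people with PACS are needed to be reached, to recruit 100 study participants".

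**The concern.** Two faces out of six lead to the IG and four to the ACG, so the rule is 1:2. The sample size is built on 1:1. Both statements are in the current text and cannot describe the same trial of 132 patients.

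The IG is the arm that receives the 3-day assessment, and several analyses depend on its size:

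- the randomised comparisons for Hypotheses 3 and 5;
- the propensity score matching with the comparison group;
- the validation of the online screening against the assessment result.

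A smaller IG weakens all three. The stated power starts at only 68%, so there is little margin to lose.

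**Working it through.** **Inputs.** From Sample size planning: two-sided alpha 0.05, power 68%, N = 132 as 66 + 66, d = 0.15, repeated-measures within-between interaction. From Evaluation concept: P(IG) = 2/6 = 1/3 and P(ACG) = 4/6 = 2/3.

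**1. The plan's own 68%.** The stated inputs do not fix this figure, because the number of measurements (m) and their correlation (ρ) are not given.

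- A plain two-group comparison with d = 0.15 and 66 per arm has power of 13.6%.
- The repeated-measures form uses a noncentral F with λ = f²·N·m/(1 − ρ). Some settings come close to 68%:
  - f = 0.15, m = 2, ρ = 0: λ = 0.0225 × 132 × 2 = 5.94, power 67.7%.
  - f = d/2 = 0.075, m = 3, ρ = 0.7: λ = 0.005625 × 132 × 3 / 0.3 = 7.43, power 67.8%.

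The 68% is therefore neither confirmed nor refuted. It is taken below as the plan's baseline, and the loss is stated relative to it.

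**2. IG size under the die.** The IG count follows Binomial(132, 1/3).

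- Mean: 132/3 = 44, leaving 88 in the ACG.
- 95% range: 34 to 55.
- P(IG ≥ 66) = 0.000056, about 0.006%.

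**3. Information in the IG-ACG contrast.** For a fixed total it is proportional to the product of the arm sizes: (44 × 88)/(66 × 66) = 3872/4356 = 8/9 = 0.89. The general form 4p(1 − p) with p = 1/3 gives the same value.

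**4. Power after scaling.**

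- Normal scale: 1.960 + 0.468 = 2.428 corresponds to 68%. Then 2.428 × √(8/9) = 2.289, less 1.960 is 0.329, so power is 62.9%.
- Noncentral F, calibrated to exactly 68%: λ runs from 5.98 (2 waves) to 10.5 (6 waves). Multiplying by 8/9 gives power of 62.9% down to 62.0%.
- The two settings in step 1 give 62.6% and 62.3%.
- At the ends of the 95% range for the IG, power on the normal scale is about 56% (IG = 34) and 67% (IG = 55).

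**5. Non-randomised patients placed in the ACG.** Their number is not stated. As an assumption, suppose 10% to 30% of the 132 are of this kind. The expected IG is then 132 × 0.9/3 = 40 down to 132 × 0.7/3 = 31. Power is about 60% to 54% if they are analysed in the ACG, or 58% to 48% if they are excluded.

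**6. Totals that would repair the plan at 1:2.**

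- To keep 68%: 132 × 9/8 = 148.5, so about 149 (about 50 IG, 99 ACG).
- To expect 66 in the IG: 66 × 3 = 198 (66 IG, 132 ACG), with power of about 80%.

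**The case against.** The strongest reply is that 132 is called required, not a stopping point. If 66 is read as a minimum per arm, about 198 randomised patients would meet it at 1:2 and power would exceed 68%. The two recruitment routes add up to 100 + 2500 × 0.2 × 0.2 = 200, and 200/3 is about 67. Those yields are illustrations that could be scaled up, so they do not show that 66 is out of reach. This part stands: the shortfall is conditional on a total of 132. But 132 is the only total the article states. Nowhere does it set 198 or recruitment until the IG reaches 66. The physician route counts people screened, and the media arithmetic also ends at taking part in the screening, with no allowance for negative screens, ineligibility or refusal. Even on this reading, 66 and 66 out of 132 remains wrong as written.

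Three further points are fair:

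- The power loss from the ratio alone is only about 5 to 6 points, and unequal allocation does not bias the comparison.
- The 68% cannot be verified, so the figure after correction inherits that uncertainty.
- Non-randomised patients are marked and can be separated. They do not change the ratio among those randomised, and matter here only if they count towards the 132.

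None of these removes the contradiction.

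**Conclusion.** The concern holds. The allocation rule and the arm sizes contradict each other. At the stated total of 132, the expected IG is 44 instead of 66, and 66 is practically unattainable. Power for the same effect is about 62–63% instead of 68%. These results rest on the total staying at 132, a fair die applied as written, and the plan's own 68% as baseline. The size of the loss hardly depends on the number of waves. Patients placed in the ACG without randomisation widen the imbalance if they count towards the 132.

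**What to change.** Make Evaluation concept and Sample size planning state the same ratio. The options are:

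1. **Keep the die and N = 132.** Restate the arms as about 44 IG and 88 ACG, with power about 62–63% for the same effect. The cost is wording and a stated power 5 to 6 points lower.
2. **Change the rule to 1–3 for IG and 4–6 for ACG,** if clinic capacity allows. The existing sample size statement then stands. No extra patients are needed, but the expected number of 3-day assessments rises from 44 to 66. If enrolment has already begun, record the date of the change and account for the two periods in the analysis.
3. **Keep the die and raise the total.** About 149 (17 more) restores 68%. About 198 (66 more) gives an expected IG of 66.

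Whichever is chosen, give the total and both arm sizes, and say that patients allocated without randomisation do not count towards them. Stating the number of measurements and the correlation used in the power calculation would let readers check the revised figure.
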